### Control Group

The control group will consist of standard of care for preoperative management of obese patients undergoing elective non-bariatric surgery without prescription of a specific preoperative weight loss intervention. Currently, there are no standardized interventions aimed at optimizing obese patients prior to undergoing non-bariatric surgery. These patients will routinely receive counselling from their surgeon at the time of their preoperative clinic visit targeted towards preoperative weight loss recommendations. Recommendations are not standardized, nor evidence based. There is no intervention lasting beyond counseling at this visit. Patients will not receive prescriptions for preoperative VLEDs, any other weight loss supplement or medication, or any physical activity intervention aimed at promoting weight loss prior to surgery.

## What are the proposed practical arrangements for allocating participants to trial groups?

Patient recruitment will occur at Hamilton Health Sciences, St. Joseph’s Healthcare Hamilton, and Kingston Health Sciences. All surgeons who perform elective non-bariatric surgery at these sites will be made aware of the study via workshops and internal communications. Patients will be identified by the surgeons, their administrative assistants, and/or study investigators at the time of referral, at the time of their initial preoperative consultation, or some time following their initial preoperative consultation. Surgeons and/or other clinicians within a patient’s circle of care will introduce the study to participants at the time of their preoperative visits or sometime thereafter. Patients may also reach out directly to study investigators via the contact information provided on the study poster should they choose. Patients meeting inclusion criteria based on a review of their electronic medical record, which will only be accessed by persons within the circle of care or researchers that have obtained permission from the patient, will have their contact information (i.e., email and phone number) recorded and provided to designated research personnel at the time of their initial surgical consultation in clinic. This email contact information will then be passed into a novel automated clinical trials platform developed by Phelix AI©. This platform will automatically send an electronic version of the written informed consent document to the patient as well as a link to schedule an appointment in the following 1-2 days with the research team to discuss the informed consent document via telephone. If the Phelix AI© platform identifies that the patient does not have an accessible email address, this will trigger a notification to the research team and prompt them to call the patient by telephone. At the time of initial contact between the study personnel and patient, the study will be introduced, eligibility will be confirmed. Patients will be provided with the opportunity to ask questions about the previously circulated ICF, and if they have yet to review the document, they will review the document in its entirety with the research team at the time of the telephone contact. If, at the end of this process, patients are understanding of the material risks and benefits of participation, and wish to be enrolled in the study, they will sign the ICF and subsequently be randomized to one of the two arms in this parallel RCT. Following ascertainment of written informed consent, patients will be randomized via a web-based randomization system (randomization.net) in a 1:1 fashion to receive either standard of care plus preoperative VLED or standard of care alone. Randomization will be according to variable block sizes of four and six and will be stratified according to centre.

Individuals with literacy, visual, and hearing issues will be included in the present study. As a research team, we will ensure that the ICF is written in lay language to a level that is understood by the majority of participants. For potential participants who have literacy issues, we will review the ICF and any other study-related questions in detail with them and any family member(s) or friend(s) with whom they would like to review this information with. If the participant demonstrates an understanding of the study following this review, they will be eligible to participate should they voluntarily choose to. For potential participants with visual issues, the ICF will be reviewed verbally with them in detail by a member of the study team in the presence of any family member(s) or friend(s) that the patient chooses. If the participant demonstrates an understanding of the study following this review, they will be eligible to participate should they voluntarily choose to. Lastly, for potential participants with hearing issues, the ICF will be given to them in written format and they will have the opportunity to review the form with the research team and their family member(s)/friend(s). If the participant demonstrates an understanding of the study following this review, they will be eligible to participate should they voluntarily choose to.

The aforementioned automated clinical trials platform developed by Phelix AI© is a novel platform that automates the “patient research journey”. The research team will input the patient contact information into the Phelix AI© platform and the platform will then automatically start patients along their journey. The specific tasks that this platform will perform for the purposes of this trial include: 1) sending the ICF document; 2) scheduling a telephone follow-up with researchers to discuss the ICF document and complete the informed consent process; 3) send reminders to patients at the 1-week and 2-week points of the intervention period to remind patients to adhere to the study protocol; 4) schedule a post-intervention follow-up appointment with the research team; 5) send a follow-up email to patients two weeks after their scheduled surgery to ascertain whether any adverse events have occurred and whether they have required any care outside of the hospital in which they underwent their index operation; 6) schedule the 30-day postoperative visit with the research team. Neither this platform nor the company will retain or store any patient or research information asides from the patient email address for contact throughout the trial. Phelix’s network and services are cloud native (i.e., built on and benefit from the security measures provided by Google’s Cloud Platform (GCP)). Phelix classifies email address as Personal Data. All data, including Personal Data, is at all times hosted on Canadian servers and resources on Google Cloud Platform. Phelix does not access, share or process Personal Data beyond what is minimally required to enable customers access their Phelix services.  Email addresses used by your organization in its engagement with Phelix are not shared externally, and only shared internally on a need-to-know basis among the Phelix personnel (i.e., the researchers) with whom you will interact by email. Otherwise, at all times, whether in transit or at rest, email addresses are treated as any other Personal Data stored on Phelix, and will be anonymized, encrypted, and securely hosted.

The technology used to design this platform has been ported from the healthcare administrative platform that Phelix AI© has developed. This is widely used across the United States and Canada to handle personal health information in a safe and efficient way alongside electronic medical records such as Oscar Pro and Accuro. Namely, this technology has been used to triage referrals, pull information from faxed consultations, schedule appointments, schedule investigations, and more. Further information on Phelix AI© and their health administrative platform can be found on their website: <https://www.phelix.ai/>.

## What are the proposed methods for protecting against sources of bias?

This trial will be randomized with variable block sizes which will protect against selection bias. In addition, surgeons, outcome assessors, and data analysts will be blinded to treatment allocation in order to reduce the risk of selection bias, measurement bias, and detection bias. Blinding of outcome assessors will be achieved via the establishment of an Independent Outcomes Adjudication committee. Given the nature of the intervention, we will be unable to blind patients which may raise the possibility of recall bias during reporting of symptom and quality of life questionnaires at the one-month follow-up. We will aim for completeness of follow-up in all randomized patients which will protect against imbalance of prognosis afforded by our randomization strategy. Lastly, we will limit crossovers and co-interventions through thorough documentation of the preoperative period to avoid contamination and the resultant impact on effect size estimates.

## What are the planned inclusion/exclusion criteria?

### Inclusion criteria

- Older than 18 years of age
- BMI of greater than 30 kg/m^2^
- Undergoing major elective non-bariatric surgery*.* Major surgery is defined as any operation performed under general anesthesia requiring a skin incision extending beyond the subcutaneous tissue.

### Exclusion criteria

- Undergoing bariatric surgery (i.e., gastric bypass, gastric sleeve, duodenal switch)
- Undergoing ophthalmologic or neurologic surgery
- Undergoing wide local excisions for skin and/or subcutaneous lesions
- Undergoing endoscopic surgery
- Undergoing urgent or emergent surgery
- Recently diagnosed myocardial infarction or unstable angina (i.e., within six months of assessment for trial enrolment)
- Diagnosed moderate-to-severe renal dysfunction (i.e., eGFR less than 30mL/min/1.73m^2^)
- Diagnosed severe liver dysfunction (i.e., cirrhosis, portal hypertension, hepatic encephalopathy, hepatorenal syndrome)
- Recently diagnosed alcohol or drug use disorders (i.e., excessive use of substance within six months of assessment for trial enrolment)
- Experienced a recent episode of gout (i.e., within six months of assessment for trial enrolment)
- Medical history of porphyria
- Known allergy to any Optifast® or Medimeal® ingredient (see “Optifast 900 Program” and “Medimeal Program” document)
- Enrolled in other prospective studies with similar interventions and/or outcomes. Co-enrollment may be deemed appropriate if the steering committees of the respective trials review the details of participation and agree that the studies and their interventions should not impact one another. Participation in non-interventional studies will be allowed.
- Pregnant or breastfeeding women
- Patients residing in a long-term care facility
- Patients otherwise unable to provide written informed consent

## What is the proposed duration of treatment period?

The current protocol in use at our local Bariatric Surgery Center of Excellence (i.e., St. Joseph’s Healthcare Hamilton) utilizes four doses of Optifast® 900 or Medimeal® daily and the total length varies between one and three weeks based on preoperative liver size and BMI. To standardize the approach for non-bariatric surgery, we propose an intervention period of three-weeks. Patients will start the intervention period three weeks and one day prior to their operative date, and the last day of the intervention will be the day prior to surgery. Our systematic review identified protocols varying from 0.46-26 weeks that were safe and efficacious, and thus we are confident that our intervention period is appropriate.^19^ Similarly, the current protocol in use at our local Bariatric Surgery Center of Excellence is in keeping with the findings of our systematic review in terms of VLED liquid formulation product and caloric intake target. In our systematic review and meta-analysis, Optifast® was the most commonly studied VLED liquid formulation (35.7% of included studies) and daily target caloric intake ranged from 450-1400kcal per day.^19^ As mentioned previously, the present study will also use the Optifast® 900 or Medimeal® and will aim to provide a total of approximately 900 kcal per day to participants.

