| **Feasibility Objectives** | The feasibility objectives of this trial are:   1. Determine the feasibility of recruiting patients in a timely manner across local and outside sites. 2. Determine compliance with preoperative VLEDs in obese patients undergoing elective non-bariatric surgery. 3. Determine the feasibility of completion of follow up. 4. Determine our ability to develop a network of participating sites in a multi-site initiative. 5. Determine the safety of administering preoperative VLEDs to obese patients undergoing elective non-bariatric surgery. |
| **Full Trial Objectives** | The overall trial objectives are:   1. Determine the impact of preoperative VLEDs on postoperative morbidity in obese patients undergoing non-bariatric surgery. 2. Determine the ability for preoperative VLEDs to effectively induce significant weight loss in obese patients undergoing non-bariatric surgery. 3. Determine the effect of preoperative VLEDs on intraoperative difficulty as measured by operative time, intraoperative blood loss, and surgeon perceived difficulty. |
| **Feasibility Outcomes** | The primary outcome will be feasibility for an adequately powered randomized controlled trial. Feasibility will be measured according to the following:   1. Recruitment rate: number of patients enrolled and randomized into the trial per month. A rate of 16 patients per month (4 patients per site per month) is considered acceptable. 2. Intervention compliance: Defined as the number of doses taken will be divided by the total number of doses prescribed (84) for each participant randomized to the intervention arm. A mean compliance of greater than 80% (i.e., completing 80% or more of their VLED doses), is the benchmark for feasibility in the present study. 3. Follow-up completion: Defined as completion of patients pre-VLED, preoperative, and 30-day postoperative visits and completion of the anthropometric measures and study questionnaires. A follow-up completion rate of greater than 90% will support the feasibility of a larger RCT. |
| **Full Trial Outcomes** | The outcomes for the overall trial will be:   - Overall 30-day postoperative morbidity - 30-day system-specific complications - 30-day postoperative mortality - Preoperative weight loss - Operative time - Intraoperative blood loss - Postoperative length of stay - Quality of life |

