| **Statistical Considerations for the Feasibility Study** | Feasibility Objectives: Descriptive statistics (means, medians, standard deviations, interquartile ranges, proportions) will be used to characterize the study sample. The outcomes of the pilot study are largely descriptive in nature and will focus on feasibility as opposed to statistical comparisons.  Overall Trial Objectives: We will not assess statistical significance for the overall trial clinical outcomes. However, we will calculate aggregated measures for 30-day postoperative morbidity to ensure an accurate power calculation is performed for the fully powered trial. |
| **Duration of Study Period (per patient)** | Patients will complete a course of Optifast® 900 or Medimeal® during the three weeks preceding their operative date. They will be followed throughout their index postoperative stay in hospital. They will then have follow-up at 30-days postoperatively. |

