## What are the planned trial interventions?

### Intervention Group

The preoperative VLED protocol will utilize Optifast® or Medimeal®, commercially available weight loss products. Specifically, the Optifast® 900 product will be used for this RCT. Patients will receive a three-week supply of Optifast® 900 or Medimeal®. They will be instructed to consume four packets of Optifast® 900 or Medimeal® mixed with water daily. This provides a total energy intake of 900 kcal per day. Patients will also be allowed to consume up to two-cups of low-calorie vegetables per day along with the Optifast® meal replacement product. They will be provided with a handout containing specific instructions with regards to the intervention (see “Very Low Energy Diet Instructions” document). The intervention group will receive the Optifast® 900 program or Medimeal®, as described above, in addition to standard of care for preoperative management.

Patients enrolled in the trial and assigned to the VLED group who are diabetics will be referred to a diabetes educator nurse practitioner for management of their insulin dosing and/or other anti-hyperglycemic medications throughout the duration of the intervention period.

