## How will the outcome measures be measured at follow up?

The feasibility measures will be ascertained by the number of patients recruited and the number of patients completing follow-up as recorded on a standardized form by a research assistant, as well as patient reported compliance via a patient-completed diet diary that they will complete daily during the three-week period prior to surgery. Both the treatment and control arms will complete these forms and give them to the research assistant in an opaque envelope on the date of their surgery. Patients in the control arms will be instructed to leave the form blank.

Safety data will be ascertained via a combination of patient self-reporting and electronic medical record data. Paper and/or electronic questionnaires will be used to assess the presence of adverse events at baseline, the morning prior to surgery, and at 30-days postoperatively.

Similarly, efficacy data will be ascertained via review of the electronic medical record. Electronic medical records will be reviewed on the date of surgery and at 30-days postoperatively to assess for any further adverse events and to evaluate 30-day postoperative morbidity. We will assess operative time, intraoperative blood loss, and postoperative length of stay via electronic medical records. The quality-of-life data will be ascertained at baseline, following completion of the VLED, and at 30-days postoperatively via administration of an in-person paper or electronic SF-36 questionnaire. Lastly, anthropometric data (i.e., height, weight, waist circumference, grip strength) will be measured at baseline, the morning of surgery, and at 30-days postoperatively by a research assistant blinded to treatment allocation. This will be recorded and stored via a Redcap© form created *a priori*.

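### The diet dates span 22 days, one more than the three weeks and 84 doses that the protocol prescribes

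*Protocol*

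**What the plan says.** The section on the proposed duration of the treatment period first gives the length: "we propose an intervention period of three-weeks". It then dates the start: "Patients will start the intervention period three weeks and one day prior to their operative date". The end is fixed in the same sentence, where we read that "the last day of the intervention will be the day prior to surgery".

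Other sections of the protocol use three weeks or its equivalent in doses:

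- Study Synopsis, duration per patient: the course is taken "during the three weeks preceding their operative date".
- Intervention Group: "Patients will receive a three-week supply of Optifast® 900 or Medimeal", with the instruction to "consume four packets of Optifast® 900 or Medimeal® mixed with water daily".
- Study Synopsis, Feasibility Outcomes: compliance is the proportion in which "the number of doses taken will be divided by the total number of doses prescribed (84" is the denominator. The main outcomes section gives the same 84.
- How outcomes are measured at follow-up: compliance comes from a "diet diary that they will complete daily during the three-week period prior to surgery".
- Budget justification: three weeks at about $100 a week, or $300 for each of 44 patients.

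Figure 1 gives yet another window. It places the diet in a column labelled -23 to -2, followed by a column labelled -2 to 0.

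**The concern.** The start day is an instruction that sites act on. Counted inclusively, the two dates give one diet day more than the length stated in the sentence before them, and four doses more than the compliance denominator allows.

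Two things are at stake. The first is conduct: sites may start a day later, let the product run out before surgery, or stretch the supply, although the section says the period was chosen to standardize the approach. The second is the compliance measure, a feasibility outcome with cuts at 70% and 80%. Doses taken over 22 days would be divided by a 21-day prescription.

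**Working it through.** **Inputs.** Surgery is day 0. The start is three weeks and one day earlier, and the last diet day is the day before surgery (both from the treatment-duration section). The dose is four packets a day (Intervention Group). The denominator is 84 (Feasibility Outcomes).

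**The protocol's own figure.** 3 weeks × 7 days × 4 packets = 84. It reproduces exactly.

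**The dates as written.**
- Start: -(3 × 7 + 1) = day -22. End: day -1.
- Inclusive count: 22 - 1 + 1 = 22 days.
- Packets: 22 × 4 = 88.
- Excess over the prescription: 22 - 21 = 1 day and 88 - 84 = 4 packets.

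**The dates with a start exactly three weeks before surgery.** Day -21 to day -1 inclusive is 21 days, and 21 × 4 = 84. This matches the stated length and the denominator.

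**Supply.** The protocol gives no packet count. If the three-week supply is 84 packets, 84/4 = 21 days. Starting on day -22, it lasts through day -2 and leaves nothing for day -1. In packets, that is 84/88 = 95.5% of the regimen as dated.

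**Compliance score, if doses on all 22 days are counted.**
- True daily adherence of 80%: 0.80 × 88 = 70.4 doses, scored as 70.4/84 = 83.8%, or 3.8 percentage points too high. An 84-packet supply does not prevent this, because 70.4 is below 84.
- A score of exactly 80% needs 0.80 × 84 = 67.2 doses, which is 67.2/88 = 76.4% daily adherence.
- Full adherence would score 88/84 = 104.8%, but only if 88 packets were supplied.

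**Compliance score, if the diary covers only day -21 to day -1.** With 84 packets and four taken on day -22, a fully adherent patient records 84 - 4 = 80 doses, scored as 80/84 = 95.2%. The direction of the error therefore depends on the diary layout, which is not shown.

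**Figure 1.** From -23 to -2 is 22 days inclusive and 21 elapsed. It ends on day -2, not day -1, so it matches neither the dates in the text nor a day -21 to day -1 diet.

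**The case against.** The strongest reply is that 22 is only one way to count. From day -22 to day -1 is 21 elapsed days. The follow-up section schedules an in-person visit when the diet is initiated, so day -22 might be a measurement day with full dosing from day -21. Figure 1 spans the same 21 elapsed days, which suggests that the authors counted that way in both places. The three-week length and the 84 doses leave little doubt about the intended amount, and the instruction handout and diary may carry the right days.

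Part of this stands. The count of 22 depends on both named days being diet days. The supply consequence depends on an assumed packet count. The handout and diary cannot be checked here. The rest does not rescue the text: it says the intervention period starts on the first day and calls the other its last day, it prescribes four packets daily, and nothing exempts either day.

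A reader might infer more than the protocol supports:

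- *That 84 doses, the supply or the budget is wrong.* All three follow from 21 days. The start date is what departs from them.
- *That every other place agrees on 21 days.* Figure 1 does not.
- *That Figure 1 is a second error, ending the diet two days before surgery.* Its adjacent columns share endpoints, so its labels are better read as phase boundaries.
- *That there is no effect at all on compliance.* The 83.8% example shows that there can be a small one.

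**Conclusion.** The point holds as a minor inconsistency. Read as written, with both named days as diet days, the dates give 22 days and 88 packets against a stated three weeks and 84 doses. The likely cause is an off-by-one slip in counting back from surgery.

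Its size is one day and four packets per intervention patient. Followed literally, it could leave an 84-packet patient without product on day -1, or score 80% daily adherence as 83.8%. The latter assumes that doses on all 22 days are counted. It could affect the reading of the 80% benchmark only if true mean adherence fell just below it, between about 76.4% and 80%. The protocol expects 80% to 100%, so nothing here suggests that the feasibility conclusion would change. The thresholds, budget and sample size are untouched.

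**What to change.** In the treatment-duration section, delete the words *and one day*. The diet then starts three weeks before the operative date and ends the day before surgery: day -21 to day -1, 21 × 4 = 84 doses.

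In Figure 1, only make the diet window agree with day -21 to day -1. A footnote on the intervention row would do. Keep a pre-surgery window for the measurements after the diet and do not collapse it to day 0, because that column holds the SF-36 (timed in the text only as after the diet is completed) as well as the anthropometrics. Randomization can stay at day -23.

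Check that the diet instructions handout and the diary use the same days. The cost is three words and one figure note. The 84-dose denominator, the 70% and 80% cuts, the supply, the budget and the sample size need no change. Keeping the day -22 start instead would require 88 doses, a new denominator and more product.
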